**1. BACKGROUND**

Type 2 diabetes (T2D) is a prevalent condition around the world. T2D patients are typically at an elevated risk of developing cardiovascular disease (CVD). As one of the most commonly prescribed lipid-lowering agents, statins are extensively used to mitigate the risk of CVDs in T2D patients with hyperlipidemia. However, there is a lack of consensus regarding the use of statins for primary prevention in T2D patients with advanced age, as limited robust evidence exists on statin use for CVD primary prevention among the older (75-84 years) and very old (≥85 years) T2D patients due to underrepresentation of this population in randomized controlled trials.

**2. OBJECTIVES**

To evaluate the effectiveness and safety of statin use for primary prevention against CVD and all-cause mortality in the old (75-84 years) and very-old (≥85 years) T2D patients with hyperlipidemia.

**3. STUDY DESIGN**

**Design:** target trial emulation.

**Data source:** electronic health records from the clinical management system (CMS) of the Hong Kong Hospital Authority. Reference data for the available information is provided on a monthly basis.

**4. STUDY POPULATION**

**Inclusion criteria:** The analysis will include all T2D patients aged ≥60 years with elevated low-density lipoprotein cholesterol (LDL-C) ≥2.6 mmol/L in each calendar month from January 2009 to December 2015. An LDL-C cut-off of 2.6 mmol/L is chosen as this represents the optimal treatment target for T2D patients with no prior history of CVD according to local guidelines (1).

**Exclusion criteria:** Patients who used statins before baseline, or used fibrates or any other lipid-lowering drugs classified under the British National Formulary code 2.12 before baseline will be excluded from the analysis. Individuals with a history of type 1 diabetes, CVDs, cancer, myopathies or liver dysfunction will be excluded. Patients with incomplete data for the study variables at baseline will also be excluded. Eligible patients need to have at least one follow-up visit record after baseline.

**5. STUDY OUTCOME AND FOLLOW-UP PERIOD**

**Primary outcome:** major CVDs (i.e., a composite outcome of myocardial infarction, heart failure, stroke).

**Secondary outcome:** the three CVD subtypes, all-cause mortality, and muscle-related adverse events (AEs) and liver dysfunction.

After peer review, we also analyzed the composite outcome of major CVD diseases without heart failure as a sensitivity analysis for comparison, and expanded the assessment of muscle-related AEs to include myalgia, myositis, myopathy, and rhabdomyolysis.

Case definition was based on the International Classification of Primary Care, 2nd Edition (ICPC-2) and International Classification of Diseases, 9th Revision, Clinical Modification (ICD-9-CM), or relevant clinical parameters (Appendix I: S3 Table). We excluded patients with pre-existing diagnosed outcomes of interest on or before baseline to ensure the outcome events were restricted to the new incident cases occurring after baseline. The patients with documented old MI diagnosis (ICD-9 code: 412) or late effects of cerebrovascular disease (ICD-9 code: 438.x) on or before baseline were also excluded. For consistency, these two codes were also included in the case definitions for outcome events for MI and stroke. After peer review, we also conducted a sensitivity analysis where these two codes were excluded from the case definition of outcome events for comparison

Patients will be followed up until the outcome of interest, death, or the administrative end of our study (31 December 2018), whichever occurs first. Potential bias of undiagnosed disease might exist for the participants who experienced the outcome incidence within the first year of follow-up. After peer review, we retained these patients in the main analysis and conducted a sensitivity analysis by excluding these patients to test the potential bias (2).

**6. EXPOSURE**

Statin therapy, defined as the treatment with any dose of simvastatin, atorvastatin, fluvastatin, rosuvastatin, lovastatin, pitavastatin, and/or pravastatin.

**7. COVARIATES**

Demographic characteristics (sex and age), clinical parameters plus blood profile (systolic blood pressure, diastolic blood pressure, hemoglobin A1c, LDL-C, high-density lipoprotein cholesterol, total cholesterol, and estimated glomerular filtration rate), comorbidities (hypertension, peripheral vascular disease, atrial fibrillation, chronic obstructive pulmonary disease, renal disease, dementia, obesity, and Charlson Comorbidity Index), drug history within 1 year before baseline (aspirin, insulin, oral antidiabetic drugs, β-blockers, calcium channel blockers, diuretics, and angiotensin-converting enzyme inhibitors), service utilization within the prior 1 year (Specialist Out-Patient Clinic attendance and hospitalization) and lifestyle behavior (smoking status).

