**Main analysis:** Propensity score matching will be employed to emulate the randomization of the eligible person-trials at baseline, where initiators and non-initiators will be matched in a 1:1 ratio within each age group (60–74, 75–84, ≥85 years). The matching factors included the aforementioned covariates and the baseline calendar month. The intention-to-treat (ITT) and per-protocol effects on the prevention of CVDs and all-cause mortality will be estimated in the emulated target trials in the three age groups. The ITT analysis will compare the risk for outcome incidence between statin initiators and non-initiators, as defined by their treatment strategy at baseline. The hazard ratio will be estimated by fitting a pooled logistic model for the outcome incidence, including the indicators of the assigned strategy (statin initiation at baseline), follow-up period (linear and quadratic terms), and the aforementioned covariates at baseline. The per-protocol analysis will compare risks for the outcomes of interest between continuous users and those who never use statins during the follow-up period, where the person-trials will be artificially censored if participants deviate from their assigned strategy unless they develop an indication or contraindication for statin therapy. To adjust for selection bias resulting from the artificial censoring process, each person-trial will be weighted at each time point by the inverse probability of receiving their assigned treatment strategy, conditional on baseline and time-varying covariates. The pooled logistic model will be fitted to predict the probability of receiving statin therapy at each time point. The last observation carried forward method will be employed to handle missing values in time-varying clinical parameters during the follow-up period. To adjust for potential bias arising from competing events (i.e., death), each person-trial will be additionally adjusted by a time-varying inverse probability weight of not dying. As the treatment strategies in the per-protocol analysis described above are adaptive to the time-varying clinical characteristics (i.e., LDL-C levels and the occurrence of any subtypes of CVDs), we adopted the non-stabilized inverse probability weight, rather than stabilized weight, for estimation of the per-protocol effect after peer review. This change of analytical choice aims to avoid the potential bias introduced by the numerator of stabilized weight. Finally, a pooled logistic model will be fitted to estimate the hazard ratio for outcomes between continuous statin therapy and never using statins during the follow-up period, incorporating the indicators of the assigned treatment strategy, month of follow-up, and baseline covariates, with adjustment for non-stabilized weights as mentioned above. The E-value was calculated to assess the robustness of the estimated results to the potential unmeasured confounding. The absolute risk of the outcome incidence will be estimated by fitting the aforementioned pooled logistic model for causal effect estimation, incorporating product terms between the treatment indicator and time.

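### No liver test is among the listed covariates, so the liver-dysfunction comparison is open to residual confounding of unknown size

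*Protocol*

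**What the plan says.** Protocol section 7 (Covariates) gives the measured variables as "clinical parameters plus blood profile (systolic blood pressure, diastolic blood pressure, hemoglobin A1c, LDL-C, high-density lipoprotein cholesterol, total cholesterol, and estimated glomerular filtration rate" and the comorbidities as "hypertension, peripheral vascular disease, atrial fibrillation, chronic obstructive pulmonary disease, renal disease, dementia, obesity, and Charlson Comorbidity Index". It names no liver enzyme, no bilirubin and no separate liver condition.

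Section 8 (Main analysis) matches initiators to non-initiators on these covariates plus the baseline calendar month, and enters them again as baseline terms in the pooled logistic model. The per-protocol weights are conditional on baseline and time-varying covariates; the time-varying set is not itemised.

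Liver status appears in three other places:

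- Section 4, as an exclusion: "Individuals with a history of type 1 diabetes, CVDs, cancer, myopathies or liver dysfunction will be excluded".
- Section 5, among the secondary outcomes: "the three CVD subtypes, all-cause mortality, and muscle-related adverse events (AEs) and liver dysfunction". Cases are identified by diagnostic codes "or relevant clinical parameters (Appendix I: S3 Table"; that table is not in the document at hand. Section 5 also states: "We excluded patients with pre-existing diagnosed outcomes of interest on or before baseline".
- Section 8, by implication, in the per-protocol rule under which person-trials are "artificially censored if participants deviate from their assigned strategy unless they develop an indication or contraindication for statin therapy".

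**The concern.** By excluding prior liver dysfunction and exempting contraindications from artificial censoring, the protocol accepts that a patient's condition, liver status included, can govern statin use. The variable most likely to carry that influence among the patients who remain, a liver test result below the exclusion level, is missing from the list that is meant to make the arms comparable.

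Matching on lipids, blood pressure and HbA1c balances the reasons to start a statin. It does not directly balance a reason to hold back that also predicts the liver outcome. If non-initiators carry more mild liver abnormality, their later rate of liver dysfunction is raised for reasons unrelated to treatment, and a modest hepatic effect of statins could be masked. Safety is part of the objective in section 2, and a null liver result in the oldest groups could be read as reassurance.

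**Working it through.** **Comparing the sections.** The protocol gives no liver event rate, event count or liver-test distribution, so it has no figure to reproduce. The textual check is as follows.

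1. Is a liver test in the listed covariates? No (section 7).
2. Is that list the adjustment set? Yes for matching and for baseline terms in the outcome model (section 8). No other set is given for safety outcomes. Section 8 first speaks of effects on cardiovascular disease and mortality and later, more broadly, of the outcomes of interest. I assume that the liver outcome follows the same models.
3. Does the exclusion close the gap? It removes recorded disease and, if the laboratory criteria of the S3 Table are applied at baseline, values beyond those criteria. Milder values and patients never tested remain.
4. Does the Charlson index close it? It is a comorbidity score, not a laboratory value, and patients with a history of liver dysfunction have already been excluded.
5. Do the sensitivity analyses close it? Analysis (2) addresses confounding by indication through familial hypercholesterolemia. Analysis (6) drops participants with the outcome in the first year, which helps with undiagnosed disease at entry but does not balance liver tests between arms. None of the ten is aimed at confounding by contraindication.

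**Possible size, on assumed inputs.** For one omitted binary confounder, the approximate multiplier on the statin–liver hazard ratio is

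[1 + p1(RR − 1)] / [1 + p0(RR − 1)]

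where p1 and p0 are the prevalences of mildly raised liver tests in initiators and non-initiators after matching, and RR is their effect on later liver dysfunction. All three are assumptions.

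| p1 | p0 | RR | Calculation | Multiplier |
|---|---|---|---|---|
| 10% | 10% | any | equal prevalence | 1.00 |
| 8% | 10% | 2 | 1.08 / 1.10 | 0.98 |
| 10% | 15% | 3 | 1.20 / 1.30 | 0.92 |
| 8% | 15% | 3 | 1.16 / 1.30 | 0.89 |
| 10% | 20% | 3 | 1.20 / 1.40 | 0.86 |
| 5% | 15% | 5 | 1.20 / 1.60 | 0.75 |
| 5% | 20% | 4 | 1.15 / 1.60 | 0.72 |

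At a multiplier of 0.89, a true hazard ratio of 1.12 would appear as 1.12 × 0.89 = 1.00. If the matched covariates already equalise mild liver abnormality, the multiplier is 1.00 and there is no bias.

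**The case against.** The strongest reply is that much of the problem may already be handled, and several points in it stand.

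- The overt contraindication is removed by restriction. If the S3 Table sets a laboratory threshold and the exclusion uses it, what remains is only the range below it, plus untested patients. A reader might infer that the liver comparison simply is confounded. The documents show an opening for residual confounding, not that it occurs.
- A reader might infer that the per-protocol weights contain nothing on the liver, so that users who stop as their enzymes rise are censored just before the outcome. Section 8 never equates the time-varying set with section 7. It even names the occurrence of cardiovascular events as a time-varying characteristic, and section 7 does not list that. The full weight specification may stand in an analysis plan that is not shown. The mechanism could in any case affect only the per-protocol analysis, and only stops made before a contraindication is recorded.
- A reader might infer that every mechanism flatters statins. That is not established. Patients without a baseline test count as liver-free in both arms. If initiators are tested more often after starting, prevalent or trivial abnormalities surface more often in the statin arm and the bias runs toward harm.
- Obesity, HbA1c, Charlson index, antidiabetic drugs and service use are matched and may carry part of the imbalance.
- An E-value is planned, and sensitivity analysis (6) is aimed at undiagnosed disease.

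The reply does not dispose of the point. The E-value describes how strong an unmeasured confounder would have to be; it removes none of it. Analysis (6) leaves the arms unbalanced on liver tests. And because case definitions may draw on clinical parameters, this confounder may well be in the records and need not be left unmeasured.

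**Conclusion.** The point holds in limited form. The listed covariates used for matching and baseline adjustment include no liver test, so the liver-dysfunction comparison is open to residual confounding by sub-threshold or unrecorded abnormality. The likely direction, if prescribers avoid statins when tests are raised, is toward apparent liver safety; differential testing after baseline could offset or reverse it.

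The size cannot be fixed from the documents. The multiplier of 1.00 to about 0.72 rests wholly on assumed prevalences and risk ratios and includes no bias at all. How much room is left depends on the laboratory criteria in the S3 Table and on whether the baseline exclusion applies them.

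A reader might carry this over to the main findings. The documents do not support that: liver dysfunction is one secondary outcome, and the argument does not reach the primary cardiovascular outcome. This is an inexpensive improvement to a stated safety analysis, not a defect in the core design.

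**What to change.** For the liver outcome only, and where liver tests are recorded:

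1. Add the last baseline liver enzyme value to the propensity score and the outcome model, with an indicator for having been tested in the prior year. The indicator keeps untested patients from being lost under the complete-data rule in section 4.
2. Include the time-varying liver enzyme value in the per-protocol weight model if it is not already there, and list the time-varying covariates so that a reader can tell.
3. Repeat the liver analysis in person-trials with a normal liver test in the year before baseline.

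The cost is re-matching and re-fitting for one outcome. The restricted check will have fewer person-trials, mainly at age ≥85, and its estimates there will be less precise.

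If liver tests are not available in the records, state the limitation and do not present a null liver result as evidence of safety.

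### Diabetes duration, retinopathy, neuropathy and albuminuria are not among the covariates, so diabetes stage is only partly controlled in a cohort made up entirely of T2D patients

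*Protocol*

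**What the plan says.** The protocol's Section 4 restricts the cohort to "all T2D patients aged ≥60 years with elevated low-density lipoprotein cholesterol (LDL-C) ≥2.6 mmol/L", so every patient has diabetes.

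Section 7 is the only place where covariates are listed. The clinical and laboratory items are "clinical parameters plus blood profile (systolic blood pressure, diastolic blood pressure, hemoglobin A1c, LDL-C, high-density lipoprotein cholesterol, total cholesterol, and estimated glomerular filtration rate". The comorbidities are "hypertension, peripheral vascular disease, atrial fibrillation, chronic obstructive pulmonary disease, renal disease, dementia, obesity, and Charlson Comorbidity Index". Drug history over the year before baseline covers "aspirin, insulin, oral antidiabetic drugs, β-blockers, calcium channel blockers, diuretics, and angiotensin-converting enzyme inhibitors". Age, sex, service use and smoking complete the list.

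Section 8 uses this list at each step:
- Propensity match: "The matching factors included the aforementioned covariates and the baseline calendar month".
- ITT pooled logistic model: indicators for strategy, "follow-up period (linear and quadratic terms), and the aforementioned covariates at baseline".
- Per-protocol weights: the "inverse probability of receiving their assigned treatment strategy, conditional on baseline and time-varying covariates". The final per-protocol outcome model also includes the baseline covariates.

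Section 8 also plans an E-value for unmeasured confounding and treats ages 60-74 as a benchmark for the validity of the emulation. Of its ten sensitivity analyses, the one aimed at confounding by indication excludes patients with familial hypercholesterolemia.

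**The concern.** When everyone has T2D, how long a patient has had it and what damage it has done are among the main ways in which patients can differ in cardiovascular and mortality risk. Stage may plausibly also bear on whether a statin is started.

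The design leaves room for this. Eligibility is assessed month by month from 2009 to 2015, and anyone with earlier statin use is excluded. An eligible non-initiator may therefore be newly diagnosed, or may have had diabetes for many years without a statin. Matching on calendar month aligns calendar time, not time since diagnosis. Two patients with the same age, HbA1c and drug history can receive the same propensity score at different stages of disease.

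Any imbalance in stage that the listed covariates do not absorb would bias the ITT hazard ratio in each age group. It would also carry into the per-protocol estimate, because those models start from the same matched sample and the same baseline covariates.

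**Working it through.** **Step 1. Is stage measured?** Each marker was checked against Section 7 and the rest of the protocol.

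| Marker of diabetes stage | In the covariate list? | Elsewhere in the protocol? |
|---|---|---|
| Time since T2D diagnosis | No | No |
| Retinopathy, neuropathy | No | No |
| Albuminuria | No | No |
| Kidney function / kidney disease | Yes (eGFR, renal disease) | – |
| Current glycaemic control | Yes (HbA1c) | – |
| Treatment step | Partly (insulin and oral drugs, prior year) | – |
| Summary comorbidity | Yes (Charlson index, components not given) | – |

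Duration, the non-renal microvascular complications and albuminuria are absent. The kidney side is at least partly covered, and several other items are indirect markers.

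**Step 2. Does another planned analysis close the gap?** None of the ten sensitivity analyses concerns diabetes duration or severity. The E-value states how strong a confounder would have to be; it adjusts for nothing.

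**Step 3. How large could the effect be?** The protocol gives no figure to reproduce and no data on stage, so every input here is an assumption. For a binary marker of advanced diabetes left unbalanced after matching and adjustment:

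bias factor = (1 + p1(RR − 1)) / (1 + p0(RR − 1))

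Here p1 is the prevalence in initiators, p0 the prevalence in matched non-initiators, and RR the marker's association with the outcome given the listed covariates. Take p1 = 0.30:

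| RR | p0 = 0.35 | p0 = 0.40 | p0 = 0.45 | p0 = 0.50 |
|---|---|---|---|---|
| 1.2 | 0.991 | 0.981 | 0.972 | 0.964 |
| 1.5 | 0.979 | 0.958 | 0.939 | 0.920 |
| 2.0 | 0.963 | 0.929 | 0.897 | 0.867 |

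- Smallest shift: (1 + 0.30×0.2)/(1 + 0.35×0.2) = 1.06/1.07 = 0.991, about 1%.
- Largest shift: (1 + 0.30×1.0)/(1 + 0.50×1.0) = 1.30/1.50 = 0.867, about 13%.

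If initiators are the ones with more advanced disease, swap p1 and p0. The factors become the reciprocals, from 1.07/1.06 = 1.009 to 1.50/1.30 = 1.154.

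**Step 4. Scale against the E-value.** For a hazard ratio below 1, treated as a risk ratio, E = 1/HR + √[(1/HR)(1/HR − 1)].

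| HR | 0.95 | 0.90 | 0.85 | 0.80 |
|---|---|---|---|---|
| E-value | 1.29 | 1.46 | 1.63 | 1.81 |

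For HR 0.90: 1.111 + √(1.111 × 0.111) = 1.46. If the observed benefit is modest, a moderate confounder could therefore matter. These hazard ratios are illustrative and are not study results.

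**The case against.** The strongest reply is that much of diabetes stage is already captured. HbA1c, insulin, oral antidiabetic drugs, eGFR, renal disease, peripheral vascular disease, hypertension, the Charlson index, hospitalization and specialist clinic attendance all plausibly track it. They enter the match and then the outcome model again. Only the imbalance and risk ratio that remain after all of these count, and nothing in the protocol supports 20 points or a risk ratio of 2.0 at that stage. This stands: the 13% figure is the extreme corner of an assumed grid.

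The plan also has two general safeguards. The E-value addresses unmeasured confounding openly, and the 60-74 benchmark could reveal strong residual bias. Both deserve credit. Neither removes confounding, though, and agreement at 60-74 does not certify the 75-84 and ≥85 groups, where the relation between stage and statin initiation may differ.

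A reader might infer three stronger claims that the protocol does not support:
- **Microvascular disease is ignored and stage is uncontrolled.** eGFR and renal disease are listed, and the other proxies give partial control.
- **The bias favours statins.** This needs a claim about when in the course of diabetes statins are offered, which the protocol does not make. Starting near diagnosis and starting once complications appear would give opposite signs.
- **Oral antidiabetic drugs are a single yes/no term.** Section 7 is a prose list and does not give the coding, which a statistical analysis plan may settle.

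It is also fair to say that the protocol does not show that the records hold diagnosis dates, complication codes or albuminuria in reliable form.

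**Conclusion.** The point holds as an incomplete covariate set. It is not a contradiction or misstatement in the plan. This is also not a detail left for a later document, because the protocol fixes an explicit list and ties the matching and ITT adjustment to it. As written, diabetes stage is only partly controlled in a cohort where it is a plausible confounder, and no planned analysis tests the consequence.

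The direction is unknown. Under residual imbalances of 5 to 20 points, a reference prevalence of 30% and risk ratios of 1.2 to 2.0, the hazard ratio would shift by about 1% to 13% downward, or by the reciprocal factors upward. These inputs are assumptions, and a shift near the lower end is compatible with the proxies working well. The change is worth making because it is specific and cheap.

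**What to change.** Add the following to the propensity score, outcome and weight models:
- time since first recorded T2D diagnosis, with a flag when that first record falls at the start of the available data;
- coded retinopathy and coded neuropathy;
- albuminuria where available, with a separate 'not tested' level so that the Section 4 rule excluding incomplete baseline data does not remove untested patients.

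Re-match within each age group and re-run the ITT and per-protocol analyses. Keep the current match as a sensitivity analysis so that readers can see what the added covariates change.

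If the records do not hold these variables, state that in Section 7. Then add a quantitative bias analysis for diabetes duration, with declared ranges for prevalence and risk ratio and both directions shown.

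**Cost.** The work is deriving the variables and repeating the matching and models. T2D status is already ascertained for eligibility, and Section 5 already relies on ICPC-2 and ICD-9-CM codes, so a first-record date and complication codes are plausible to derive. Two limits should be stated. Duration is cut short for patients diagnosed before the records begin, which may affect many in the older groups. Complication codes may also be under-recorded, so an absent code does not prove an absent complication.
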